**Fig. 1 Fig1:**
[figure not shown]
Overview of the study design and course of the spatial intervention study. T0 is the final appointment of the standard diagnostic investigation at the memory clinic. T1 & T2 are additional appointments for research interviews

**Table 1 Tab1:** Endpoints, potential predictors and measuring instruments

Measured quantity	Instrument and description	Time of assessment
Ability to ‘understand’, ‘appreciate’, ‘reason’ and ‘express a choice’ as preconditions of capacity to consent	CAT-AD: adjusted version of the DCAT-PAD/MacCAT-T [20, 21] for PwAD	T1 & T2
	Semi-structured interview	
Subjective task complexity	Subscale ‘post task: subjective task complexity’ [28]	T1 & T2
	4-item-subscale	
Decisional conflicts	Subscale ‘uncertainty’ of the German version of the ‘Decisional Conflict Scale’ [29]	T1 & T2
	3-item-subscale	
Anxiety in the decision-making situation	Single item described by LeBlanc et al. [30]	T1 & T2
Age, gender		T0
Education	Single item based on German education system	T0
Severity of dementia	Mini-Mental Status Examination [31]	T0
	Screening for cognitive abilities to detect cognitive impairment or dementia	
Severity of possible depression	Geriatric Depression Scale [32]	T0
	Screening for depression in the elderly	
Perceived sense of belonging to home	Selection of items from Meaning of Home Questionnaire [26, 27]	T0
	Adjusted for people with dementia & validated during the project	
	Guided interview	
Need of autonomy for medical decisions	Single item described by Strull et al. [33]	T0
Health literacy	Single item described by Morris et al. [34]	T0

As in our previous studies, the presentation of information will be standardised for both the intervention and the control settings in order to ensure as much consistency as possible in everything apart from the ‘place’. Consequently, all support strategies that have proven to be effective in our own and international studies (e.g., elaborated plain language, key word list, time of day: 8–15 o’clock, person-centred attitude), will be used in both places (as recommended in the current AWMF-S2k-guideline “Einwilligung von Menschen mit Demenz in medizinische Maßnahmen”; for a summary of available evidence on SDM for PwAD, see [7, 19]).

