#### Statistical analysis

A linear mixed model with place, period, and interaction of place and period as fixed effects and patient as a random effect will be used to analyse the primary endpoint. We will check for carryover by testing the interaction between place and period. If there is no significant interaction effect, differential carryover can be neglected. Otherwise, statistical analysis will be stratified by period, whereby the main analysis will be restricted to the first period, and data from the second period will be used for sensitivity analysis.

An exploratory investigation of the impact of the place the decision is made on subjective task complexity, decisional conflicts and anxiety will be based on a model that is analogous to the main analysis.

Furthermore, both linear mixed models will be extended to include an exploratory analysis of potentially confounding, moderating, and mediating variables.

The relationship between the place the decision is made, and the other secondary endpoints will be explored by conducting two-sample comparisons between the sequence groups in a two-step procedure based on Wilcoxon-Mann–Whitney tests, consisting of a pretest for differential carryover and a main test for the location effect. This is essentially equivalent to the mixed model approach but assumes no particular probability distributions and does not permit inclusion of covariates. If the pretest is significant, the main test will only be performed on data from the first period.

The features of the patient sample will be summarised descriptively. Absolute and relative frequencies will be used for categorical variables, and mean, standard deviation, minimum, maximum, and quartiles for metric variables.

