#### Calculation of sample size

From a recent trial evaluating SDM strategies for patients with dementia (EmMa project) [9], the MacCAT-T subscale scores of the 30 patients with Alzheimer’s disease (14 in the intervention, 16 in the control group) were used to define the relevant standardised location effect for the sample size calculation. While the SDM strategies in EmMa project only increased scores on the “understanding” subscale of the MacCAT-T, we expect that in our trial, the support of the familiar environment of the patient’s home will rather influence the “reasoning” subscale. Thus, we anticipate that as a result of the DECIDE intervention, the change in the reasoning score will be similar to the standardised effect of 0.582 found for understanding in EmMa project.

Due to memory limitations in the study population, we do not expect any substantial carryover effect. The relevant quantity for the sample size calculation will therefore be the location contrast estimated from both periods. However, although unlikely to be detected in a cross-over design powered for the main effect of the place the decision is made, slight differential carryover will still bias the effect. Hence, the sample size should allow us to compensate for power loss due to undetected differential carryover of up to 20% of the spatial intervention effect.

Use of a cross-over design further means that only intra-individual variance must be taken into account. The stronger the correlation between a patient’s two observations, the smaller the intra-individual variance and the smaller the necessary sample size. Although we expect some positive correlation, we will assume uncorrelated observations to be on the safe side.

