Based on these assumptions, and with a two-sided significance level of α = 5%, the power.t.test () function of the R stats package (version 4.0.2) results in a total sample size of 80 patients, 160 observations, for a power of 90%. If recruitment difficulties arise, 80% power will still be achieved with 60 patients and 120 observations. If – as is to be expected – a positive correlation exists between the same patient’s measurements, even fewer patients will suffice to reach 80% power. For example, assuming a within-patient correlation of 0.2, the inclusion of 48 patients and 96 measurements will mean the power is still 80%. If a significant proportion of patients can only be studied once, the analysis could be restricted to the first observations. However, if 80 first measurements are available, the power for detecting the location effect will be reduced to 58%. In this case, we would try to include a further 16 patients and thus achieve 80% power.

Since a two-step evaluation procedure based on a linear mixed model will be used to analyse the primary endpoint, we verified the sample size in a simulation of the procedure with 10,000 analysis runs per scenario. Based on the relevant standardised effect (see above) and the variance in the ‘reasoning’ scores observed in EmMa project [9], we considered four scenarios covering a range of realistic outcomes. They are presented in Fig. 2. The simulation confirms the sample sizes obtained from the t-test formula.

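### Any first-period main analysis is a between-patient comparison, yet it is left unadjusted for the MMSE score already collected at T0

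*Protocol article*

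**What the plan says.** The Statistical analysis section lists the terms of the primary model: place, period, their interaction, and a random patient effect. If the interaction is significant, "the main analysis will be restricted to the first period, and data from the second period will be used for sensitivity analysis". The Missing data and Calculation of sample size sections describe a second route to first-session data, for the case in which too many patients can be seen only once. For that route alone, the sample size section gives 58% power with 80 first measurements and continues: "In this case, we would try to include a further 16 patients and thus achieve 80% power".

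Baseline variables come in only later: "both linear mixed models will be extended to include an exploratory analysis of potentially confounding, moderating, and mediating variables". One of them is severity of dementia. Table 1 assigns it to the Mini-Mental Status Examination at T0 and describes that test as "Screening for cognitive abilities to detect cognitive impairment or dementia". Under Data collection, T0 comes before assignment to a sequence. Under Participants, patients with severe dementia (clinical diagnosis or MMSE below 10) are excluded.

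**The concern.** With both sessions observed, each patient is their own control, and a T0 covariate adds nothing to the within-patient place contrast. Restricting the analysis to the first period removes that protection. Period, interaction and the random effect drop out, home is compared with clinic in different patients, and all between-patient variation enters the error term.

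The protocol's own premises suggest that T0 severity is prognostic. The Background says that cognitive decline can cost patients their capacity to consent, and the secondary endpoints section lists severity of dementia among the suspected moderators, mediators and confounders. The covariate is measured before assignment and collected at T0 as part of the baseline assessment. Leaving it out of the fallback main analysis loses power where the design has least to spare. It also means that a chance difference in severity between two groups of about 40 stays in the primary result.

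**Working it through.** **Inputs.** From Calculation of sample size: test "with a two-sided significance level of α = 5"%; standardised effect, with "the change in the reasoning score will be similar to the standardised effect of 0.582 found for understanding in EmMa project"; a sample size meant to "compensate for power loss due to undetected differential carryover of up to 20% of the spatial intervention effect"; base-case correlation between sessions, where "we will assume uncorrelated observations to be on the safe side"; alternative within-patient correlation 0.2. Allocation is 1:1, so 80 patients give 40 per place in the first period. The correlation rho between T0 MMSE and the reasoning score is not in the protocol, so a range is assumed.

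**Formula.** Two-sample t-test power from the noncentral t distribution, with n per place, noncentrality d × √(n/2) and 2n − 2 degrees of freedom. With the covariate, d becomes d/√(1 − rho²) and one degree of freedom is lost.

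**1. The plan's own figures.** Carryover of 20% that affects only the second period shifts the two-period contrast by half of that, so d = 0.582 × 0.9 = 0.524.
- Crossover, 80 per place: 90.9% (stated 90%). 60 per place: 81.2% (stated 80%). 48 patients with correlation 0.2: 81.1% (stated 80%). These reproduce.
- First period, 96 patients (48 per place), d = 0.582: 80.6% (stated 80%). This reproduces.
- First period, 80 patients (40 per place): 72.9% at d = 0.582, 63.8% at 0.524, and 53.9% at 0.466 (0.582 × 0.8). The stated 58% does not reproduce. It needs d = 0.489, and with that effect 96 patients give only 66%. So 58% at 80 patients and 80% at 96 cannot both come from one effect size. The check below is therefore run from both starting points.

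**2. Effect of adjustment, 40 per place.** Example: at d = 0.582 the noncentrality is 0.582 × √20 = 2.60. At rho = 0.4 it is 2.60/√0.84 = 2.84.

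| Assumed rho | d = 0.582 | d = 0.524 | d = 0.489 (stated 58%) |
|---|---|---|---|
| 0 (unadjusted) | 72.9% | 63.8% | 58% |
| 0.2 | 74.6% | 65.6% | 59.7% |
| 0.3 | 76.9% | 67.9% | 62.0% |
| 0.4 | 80.1% | 71.4% | about 65% |
| 0.45 | about 82% | about 73% | about 68% |

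**3. How large rho can be.** If MMSE acts equally in both sessions, it contributes rho² to the correlation between them. If the remaining within-patient correlation is not negative, rho² cannot exceed the total. Under the base case of zero, rho = 0 and the gain is nil. Under 0.2, rho is at most √0.2 = 0.45, so the gain at d = 0.582 is at most about 82 − 73 = 9 points.

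**4. Imbalance and the carryover pretest.** In an AB/BA design the place-by-period term is the difference between sequence groups. A chance imbalance in MMSE can therefore trigger the fallback and then enter the first-period estimate. This was simulated with 80 patients, no place effect, no carryover, both tests at 5% (the pretest level is an assumption), rho = 0.4 and 20,000 runs. Among trials in which the pretest was significant, the first-period place test rejected as follows:
- within-patient correlation 0.5: 52% unadjusted, 36% adjusted for MMSE;
- within-patient correlation 0.2: 41% unadjusted, 26% adjusted.

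About 5% of runs, some 1,000, reach this stage, so each percentage carries a Monte Carlo error of about ±3 points.

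**The case against.** The strongest reply is that nothing here is invalid. Order is randomised, so the unadjusted first-period contrast is unbiased over randomisation, and an adjusted estimate would be available from the exploratory extension. Both points stand, with two limits. An exploratory estimate is not the main result, and unbiasedness over all randomisations no longer holds once a pretest that responds to the same imbalance has selected the analysis.

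The benefit is also assumed rather than documented. No MMSE-reasoning correlation is given, the plan's conservative case implies no gain, and the Limitations section expects less impaired patients to take part more often, which could narrow the MMSE range. This stands, and it is why only a range can be stated. The zero correlation is adopted for safety, however, and the same section says that some positive correlation is expected.

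Reach is limited too. The plan does not expect substantial carryover, and the studied-once route is conditional.

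Finally, one could say that the covariate list belongs in a statistical analysis plan. But the article does list the model terms and does assign covariates to an exploratory role, so this is a stated choice and not an omission.

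**Conclusion.** The point holds as a cheap improvement in efficiency and robustness, not as an error of validity. Any first-period main analysis is, as written, an unadjusted comparison between patients. Prespecifying T0 MMSE would add between 0 and about 9 points of power at the planned effect with 80 patients. This rests on an assumed rho of 0 to 0.45, an equal MMSE effect in both sessions, and a within-patient correlation of at most 0.2.

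Three stronger readings are not supported:
- **That adjustment replaces the 16 extra patients.** At d = 0.582 this would need rho of about 0.40, which is not established. Starting from the plan's stated 58%, rho = 0.4 gives only about 65%, and 80% would need rho of about 0.64, above the 0.45 ceiling. The top-up also belongs only to the studied-once case; none is attached to the carryover fallback.
- **That adjustment repairs the two-stage procedure.** It removes part of the excess rejection after a significant pretest, but rates of 26% to 36% remain far above 5%.
- **That MMSE could be added to the both-period model without consequence when pairs are complete.** The within-patient place contrast is unchanged, but the place-by-period test is a between-patient contrast. In simulation at rho = 0.4 without carryover, adding MMSE changed its verdict in about 4 to 5% of trials, and that test selects the main analysis.

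**What to change.** In the Statistical analysis section, add a sentence to this effect: whenever the main analysis is restricted to first-period data, for either reason, it is a linear model of the reasoning score on place with the T0 MMSE score (continuous) as a prespecified covariate, and this adjusted estimate is the main result. Repeat the reference where the Missing data and Calculation of sample size sections restrict the analysis to first observations.

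Leave the 16-patient provision in place for the studied-once case. Separately, reconcile the 58% with the 96-patient figure. If MMSE is also wanted in the both-period model, decide that in advance, because it alters the interaction test.

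The cost is one sentence, one model term and one degree of freedom. MMSE is already collected at T0, so no extra data or visits are needed. If it proves unrelated to reasoning, the loss is negligible.

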#### Missing data

From our experience with the first part of the DECIDE project, we expect a low overall proportion of missing data in the baseline assessment and the first ACP interview, which we will handle using complete case analysis (with less than 5% of incomplete records) or multiple imputation. A higher proportion might accrue in the second interview. As this kind of missingness would still be at random (conditional of the observed period variable), it can be resolved using multiple imputation, too. Apart from this, should it turn out that too many patients are available for the first ACP interview only, we will restrict our analysis to these observations as described in the next section.

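### The missing-data fallback drops every second-session score on an undefined trigger, although the planned mixed model can keep them; missingness at random given period alone is not a sound basis

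*Protocol article*

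**What the plan says.** **Primary model.** The Statistical analysis section specifies: "A linear mixed model with place, period, and interaction of place and period as fixed effects and patient as a random effect will be used". A significant place-by-period interaction is read as carryover, and the main analysis is then confined to period 1.

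**Missing second sessions** (Missing data): the plan expects more missing data at the second interview than at the first and gives no figure. It states: "As this kind of missingness would still be at random (conditional of the observed period variable), it can be resolved using multiple imputation, too". Imputation is therefore the first resort. Beyond it there is a fallback: "should it turn out that too many patients are available for the first ACP interview only, we will restrict our analysis to these observations".

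**The same fallback again** (Calculation of sample size): "If a significant proportion of patients can only be studied once, the analysis could be restricted to the first observations". Here the protocol gives 58% power with 80 first measurements and says it would try to add 16 patients to reach 80%.

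**The concern.** There are three linked problems.

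1. *Valid data are discarded.* A mixed model with a random patient effect accepts patients with one session alongside patients with two. Deleting every second session because some are missing gives up the within-patient comparison for which the crossover was chosen.
2. *The trigger is open.* Neither passage puts a number on how many single-session patients activate the switch. Missing data says the analysis *will* be restricted; the sample size section says it *could* be. The primary estimator could thus be chosen once data are in, in a study whose assessors are not blinded.
3. *The at-random statement does not follow.* Missing values that cluster in period 2 are not thereby random within period 2. Whether a patient attends can depend on the first-session score, on dementia severity, and on whether the second session is at home or at the clinic, which differs by sequence. The protocol's own section on adherence and retention takes measures against selective drop-out linked to cognitive impairment.

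At stake are the power of the primary comparison and whether its estimator is fixed in advance.

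**Working it through.** **Inputs from Calculation of sample size.** The effect: "the change in the reasoning score will be similar to the standardised effect of 0.582 found for understanding in EmMa project". The test: "with a two-sided significance level of" 5%. The size: "results in a total sample size of 80 patients, 160 observations, for a power of 90" per cent. The allowance: "compensate for power loss due to undetected differential carryover of up to 20% of the spatial intervention effect". Within-patient correlation ρ is taken as 0 for sizing, and 0.2 in the plan's own example. The shares *m* of second sessions missing (30%, 50%, 70%) are assumptions; the protocol gives none.

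**Step 1: the plan's own figures.** A 20% carryover reduces the period-2 contrast by 20% and the two-period average by 10%, so the effect is 0.9 × 0.582 = 0.524. A two-sample t-test (noncentral t) gives 90.9% with 80 patients (stated 90%), 81.2% with 60 (stated 80%) and 81.1% with 48 at ρ = 0.2 (stated 80%). The main design reproduces.

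**Step 2: first sessions only.** With 40 patients per place, V = 2/40 = 0.050 in squared SD units. The noncentrality is 0.582/√0.050 = 2.60; with 78 df, power is **72.9%**. The stated 58% does not reproduce: 0.524 gives 63.8% and 0.466 (= 0.8 × 0.582) gives 53.9%. The stated 80% with 96 patients does reproduce at 0.582 (80.6%). This mismatch is a separate point; 72.9% is used below.

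**Step 3: all observed sessions.** Generalised least squares with 40 patients per sequence, a share *m* lacking session 2, power from noncentral t with 78 df.

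- Without the interaction: 1/V = 20*m* + 40(1 − *m*)/(1 − ρ). At ρ = 0 this is 20(2 − *m*).
- With the interaction kept and place averaged over the two periods, at ρ = 0: V = ¼[0.05 + 0.05/(1 − *m*)] = 0.0125[1 + 1/(1 − *m*)].

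| Effect 0.582, ρ = 0 | 30% missing | 50% | 70% |
|---|---|---|---|
| V, no interaction | 0.0294 | 0.0333 | 0.0385 |
| Power, no interaction | 91.8% | 88.3% | 83.4% |
| V, interaction kept | 0.0304 | 0.0375 | 0.0542 |
| Power, interaction kept | 91.0% | 84.3% | 69.5% |
| Power, first sessions only | 72.9% | 72.9% | 72.9% |

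Break-even with the interaction kept: 0.0125[1 + 1/(1 − *m*)] = 0.050 gives 1/(1 − *m*) = 3, so *m* = 2/3. At ρ = 0.2 it is about 71%. Without the interaction, power at ρ = 0.2 is 95.7%, 92.5% and 87.2%.

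**Step 4: allowing for carryover.** First sessions carry no carryover, so their 72.9% stands. Applying the full 10% dilution to the mixed model without the interaction (ρ = 0) gives 85.5%, 80.9% and 75.1%, still higher. With the interaction kept, the same dilution lowers the break-even: V must be at most 0.9² × 0.050 = 0.0405, so 1/(1 − *m*) = 0.0405/0.0125 − 1 = 2.24 and *m* is about 55%.

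**Step 5: bias.** Simulation, 5,000 runs per scenario, true effect 0.582, about 35–41% of second sessions missing, ρ from 0.2 to 0.7; the dropout patterns are assumed.

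- Dropout depending on the first score, or on first score and place: the mixed model averages 0.58. Ignoring the first score gives 0.51–0.60; complete pairs only give 0.55–0.69.
- Dropout depending on the unseen second score, at the clinic only: the mixed model gives 0.45–0.50, first sessions only 0.58. Root mean square error is still slightly lower for the mixed model: about 0.21 against 0.22 at ρ = 0.2, and 0.17 against 0.22 at ρ = 0.5.

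**The case against.** The strongest defence is robustness. The first-session contrast is a randomised comparison, untouched by carryover or by second-session dropout of any kind. Under non-random dropout the mixed model was biased and the first-session contrast was not. This stands: the fallback is inferior in precision, not in bias under every mechanism, and it should be kept in another role.

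The model as written includes the place-by-period term, and the text does not say that it is removed when non-significant. With it retained, the power advantage vanishes under heavy missingness, which is when the fallback would be used. This also stands. A reader might infer that the mixed model wins at any missing rate; that is true only without the interaction.

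The fallback is a last resort after imputation, retention measures are described, the power loss is disclosed, and the 16 added patients would bring first-session power to 80.6% at 0.582. A reader might infer that the trial simply becomes a 73%-power parallel-group study; the top-up means the documents do not support that. At equal numbers, though, the mixed model without the interaction remains more powerful, and the protocol itself expects recruitment to be hard.

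A reader might also infer that imputation will ignore the first-session score. The protocol lists no imputation variables and excludes none, and that detail may belong to the analysis plan. What can be criticised is the stated justification, which names period only.

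**Conclusion.** The concern holds in this form. The plan permits all second-session scores to be dropped on a trigger that has no number and that two passages word differently, while the model it already specifies can use those scores. At zero correlation and the full effect of 0.582, the cost is about 19, 15 and 11 percentage points of power at 30%, 50% and 70% missing without the interaction (91.8, 88.3 and 83.4 minus 72.9). With the interaction kept it is about 18 and 11 points at 30% and 50%, and the sign reverses above about two-thirds missing. The missing rates are assumptions.

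The at-random claim is unsupported as worded, but the documents do not show how much bias would result. One can construct a case: if the lowest first-session scorers drop out, 30% with the clinic second and 10% with home second, ρ = 0.5 and the first score is ignored, the place contrast shifts by −0.5 × (0.497 − 0.195)/2, about −0.075 SD. That is an illustration under assumed dropout, not a property of the plan. In the simulations, ignoring the first score erred in either direction.

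**What to change.** - Make the likelihood-based mixed model on all observed sessions the primary analysis at any level of second-session missingness. State that the place effect is estimated without the interaction term unless the plan's carryover rule applies.
- Keep the first-session contrast as a prespecified sensitivity analysis, not a replacement triggered by the data. Align the Missing data and sample size sections accordingly.
- Restate the missingness assumption as conditional on first-session score, sequence and place, site and baseline severity (MMSE, GDS), and include these in any imputation.
- Add a delta-adjusted sensitivity analysis by place.

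The cost is wording and two sensitivity analyses on data already planned for collection. The downside is that the primary estimate then relies on missingness at random given the observed data; the two sensitivity analyses are there to check that.
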